### Design and overall procedure

The project is a cluster-randomized clinical trial following Good Clinical Practice (GCP) principles. Standard Operating Procedures will be developed for key routines, and digital Client Report Files will be stored in the study technical platform provided by Karolinska Core Facilities. Study coordinators will primarily monitor data quality and routines internally. This protocol was devised according to the SPIRIT reporting guidelines [61]. Any substantial amendments to this protocol will be tracked, dated and described in trial reports.

Data will be collected at Närhälsan, the provider of public primary care in Västra Götaland, Sweden, consisting of 104 PCCs in both urban and rural areas. This project studies a naturalistic implementation effort initiated by Närhälsan, with external trainers and supervisors procured by the organization. The study will utilize a cluster-randomized design, randomly assigning PCCs to either implement PCBH immediately (EARLY) during the first 5–9-month period or act as control centers and implement PCBH during the second period (DELAYED). Period 1 starts when all PCCs in the EARLY group have scheduled starting dates during on-site consultations. Period 2 begins when all PCCs in the DELAYED group have done the same, within 5 to 9 months after the start of Period 1. Provided sufficient project resources, period 2 can be lengthened to allow for continued data collection. Patient measures will be collected up to two months before Period 1, and some organizational measures up to one year in advance, establishing a baseline for each PCC. As the project, due to the naturalistic approach, has little direct control over how well a PCC implements PCBH, the analysis plan covers several scenarios where varying degrees of model fidelity are considered (see Data analysis plan).

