### Data analysis plan

We are planning to conduct one main analysis for each of the primary outcomes at each level, a range of explorative and longitudinal analyses for the implementation-level outcomes, and several secondary analyses for the organizational- and patient-level outcomes. Primarily, we aim to confirm that the EARLY arm reaches adequate fidelity level faster than the DELAYED arm and to capture the randomized controlled effects of PCBH on organization- and patient-level outcomes when it has reached adequate model fidelity during the first implementation period (corresponding to an implemented-per-protocol perspective). We also want to evaluate the controlled effects of intending to implement PCBH regardless of what level of fidelity each PCC reaches (corresponding to an intent-to-implement perspective) and the non-controlled (i.e., not comparing the randomized groups) relation between reaching adequate model fidelity and outcomes (corresponding to an adherence-effect or dose-response perspective). No interim analyses are planned.

Implemented-per-protocol analyses:

PCCs in EARLY, from when they have reached FID3, compared to all PCCs in DELAYED, during period 1 (main analysis).As (1), but also including data from period 2 in EARLY (but not in DELAYED), to control for the event of PCCs needing extended time to reach FID3, thus lowering the power of the main analysis.

Intent-to-implement analyses:

3.All PCCs regardless of model fidelity in EARLY compared to all PCCs in DELAYED during period 1.4.As (3), but for periods 1 and 2.

Adherence-response analyses (not controlled by randomization):

5.All PCCs, regardless of arm, when in FID3 during period 1 or 2, compared to PCCs in DELAYED during period 1.6.As (5), but compared to all PCCs before they reach FID3.

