### Current trial status

Implementation period 1 started in January 2022. Patients will be included until December 31st 2023, and the last participant is expected to reach the final endpoint (one-year follow-up) in December 2024. Data analysis will begin in May 2024.

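### Secondary analyses 4 and 2 do not estimate the controlled effect they are listed under: analysis 4 dilutes it, and the data added in analysis 2 have no concurrent control

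*Protocol article*

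**What the plan says.** Under Design and overall procedure, the DELAYED centres "act as control centers and implement PCBH during the second period (DELAYED". They are therefore controls in period 1 only. Period 2 begins 5 to 9 months after period 1.

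The Data analysis plan states two controlled aims. The implemented-per-protocol group (analyses 1 and 2) is to capture the "randomized controlled effects of PCBH on organization- and patient-level outcomes when it has reached adequate model fidelity during the first implementation period". The intent-to-implement group (analyses 3 and 4) is to capture the "controlled effects of intending to implement PCBH regardless of what level of fidelity each PCC reaches".

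- Analysis 3 compares all EARLY centres with all DELAYED centres in period 1. Analysis 4 is "As (3), but for periods 1 and 2".
- Analysis 2 is "As (1), but also including data from period 2 in EARLY (but not in DELAYED"). The reason given is that centres may need longer to reach FID3, which would lower the power of the main analysis.
- Only analyses 5 and 6 stand under the heading "Adherence-response analyses (not controlled by randomization").

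Under Current trial status, period 1 started in January 2022 and "Patients will be included until December 31st 2023".

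**The concern.** **Analysis 4.** In period 2 both arms intend to implement PCBH. Analysis 2 excludes DELAYED period-2 data in so many words and analysis 4 does not, so the plain reading is that those data stay on the comparison side. The result then averages a contrast with usual care and a contrast between two implementing arms. If it is reported as the effect of intending to implement PCBH, a real effect looks smaller than it is.

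**Analysis 2.** The EARLY data added from period 2 are set against DELAYED data from an earlier calendar time. Any change over time in demand, staffing or case mix enters the estimate as if it were an effect of PCBH. The analysis nevertheless sits under an aim worded as a randomized controlled effect, and that aim is itself limited to the first period.

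**Working it through.** **Inputs.** Period 1 lasts L = 5 to 9 months (Design and overall procedure). Inclusion runs from January 2022 to 31 December 2023, about 24 months (Current trial status). Participant recruitment and power analysis gives d = 0.4, ICC 0.01, 8 and 9 centres, and 476 patients analysed.

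**The plan's own figure.** 476/0.8 = 595 and 595/0.7 = 850, as stated. With 476/17 = 28 patients per centre, SE = √[(1/8 + 1/9)(0.01 + 0.99/28)] = 0.1035. On 15 df at a two-sided 5% level (assumed, as alpha is not given), power at d = 0.40 is about 95%. That is more than the 90% aimed for: those inputs would need about 366 patients. Alpha and variation in centre size are not stated, so this is not called an error. 476 serves below only as a common yardstick.

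**Analysis 4.** Let w be the share of patients from period 1 and r the share of the effect that still separates the arms in period 2. The expected difference is 0.40 × [w + (1 − w)r].

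| Assumptions (none stated in the article) | w | r | Expected d | Power at 476 |
|---|---|---|---|---|
| Even enrolment over 24 months, same time course in both arms | 5/24 to 9/24 | 0 | 0.083 to 0.150 | 11% to 27% |
| Equal periods, full effect in DELAYED in period 2 | 1/2 | 0 | 0.20 | 44% |
| Even enrolment, DELAYED has half the effect in period 2 | 5/24 to 9/24 | 0.5 | 0.242 to 0.275 | 59% to 70% |

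The first row does not need an instant effect in DELAYED. If both arms follow the same build-up, L months apart, and it levels off before the last L months, the average difference over 24 months is L/24 of the full effect.

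**Analysis 2.** The check uses centre-by-period means with a random centre effect, ICC 0.01 and 14 patients per centre and period (28 split over two periods). A calendar trend of 0.1 to 0.2 SD between periods is assumed, with no PCBH effect. The number of EARLY centres at FID3 in period 1 is varied; all 8 contribute in period 2.

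| EARLY centres at FID3 in period 1 | Spurious difference, no period term | SE, period 1 only | SE, analysis 2 without period term | SE, analysis 2 with period term |
|---|---|---|---|---|
| 8 | 0.05 to 0.10 | 0.138 | 0.121 | 0.138 |
| 4 | 0.07 to 0.14 | 0.171 | 0.127 | 0.170 |
| 2 | 0.08 to 0.16 | 0.222 | 0.132 | 0.221 |

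Without a period term the added data tighten the interval but let the trend in. With one, precision returns to about that of period 1, because every period-2 observation comes from an EARLY centre at FID3.

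**The case against.** The strongest reply is that analysis 4 compares the arms as randomized, and that the article explains non-controlled as not comparing the randomized groups. That stands. A reader might infer that analysis 4 is invalid or no longer randomized; the documents do not support this. Its question is earlier versus later start, and what is wrong is reading it as PCBH versus usual care.

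A reader might also infer that dilution would yield a false non-inferiority claim. The article plans non-inferiority testing on the primary patient outcome if superiority is not shown, but nowhere assigns that test to analysis 4. The risk is a reason to rule the use out, not a flaw in a stated test.

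The size of the dilution depends on the enrolment pattern and on uptake in DELAYED, neither of which is given. DELAYED centres may be short of FID3 for part of period 2, which makes the loss smaller. This also stands, and is why a range is shown.

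Analysis 2 states its asymmetry and the reason for it, and calendar-time terms are model detail that an article may leave to an analysis plan. Their absence is not the point. What the article does fix is the grouping of analysis 2 with the controlled comparisons.

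**Conclusion.** The point holds for two of the five secondary analyses. Analysis 4 is a sound randomized comparison of earlier with later start, but a diluted estimate of the effect named for its group. A true d of 0.40 would appear somewhere between about 0.08 and 0.28 across the scenarios examined, each resting on assumptions about enrolment and DELAYED uptake that the article does not state. Analysis 2 adds data without concurrent controls. The bias depends on a calendar trend whose size the article does not give; a trend of 0.1 to 0.2 SD would produce a spurious 0.05 to 0.16 SD.

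It would be wrong to infer that the trial's main result is at risk from this. Main analysis 1 and analysis 3 use period 1 in both arms and are untouched by it. The point should be fixed; because both analyses are secondary, it is not critical.

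**What to change.** **Analysis 4.** Present it as earlier versus later start. Alternatively, code exposure by centre and date, so that DELAYED counts as exposed from each centre's own start, with calendar-time effects. Either way, state that neither superiority nor non-inferiority of PCBH versus usual care will be concluded from the diluted contrast. Relabelling costs only wording. Exposure coding adds model assumptions and little precision once all centres are exposed. With 14 patients per centre and period, the correlation of a centre's two means is 0.01/(0.01 + 0.99/14) = 0.124, so the SE falls only by the factor √(1 − 0.124²) = 0.99 relative to period 1 alone.

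**Analysis 2.** Move it to the group not controlled by randomization and state that its added data lack concurrent controls. A calendar-time term can be reported as a sensitivity analysis. Its downside should be acknowledged: it returns precision to about that of period 1 alone and so gives up the power the analysis was meant to recover. Borrowing DELAYED period-2 time as control would help little. Period 2 opens only once all DELAYED centres have scheduled their starts, and choosing control time by later fidelity is a post-randomization selection. Analysis 6 already compares with centres before FID3.

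No new data are needed for either change.

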#### Statistical tests

Hierarchical Linear Models and Generalized Estimating Equations will be the primary statistical methods used. Missing data will be addressed through appropriate imputation methods that align with the missing data mechanism and account for the multilevel structure of the data. Alternatively, statistical techniques capable of handling missing data, such as multilevel models, will be employed for analysis. The analyses will take into account the multilevel structure of the data, e.g. nesting patients under PCC for patient outcomes. For Health Economic Analyses, effectiveness will be estimated by the construction quality-adjusted life-years (QALYs) based on EQ-5D. Incremental cost-effectiveness ratios (ICERs) will be computed and Monte Carlo simulation with non-parametric bootstrapping will be performed to account for the uncertainty of the ICER point estimates. Cost-effectiveness acceptability curves (CEACs) will be used to explore cost-effectiveness under varying willingness to pay-circumstances.

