## Discussion

The main purpose of the current project is to strengthen the evidence base for the effects that PCBH has on implementation-, organization-, and patient-level outcomes. Implementation of a primary care model such as PCBH needs to be studied in a naturalistic setting, which reduces the possibility for rigorous research procedures and high levels of control. In addition, implementing PCBH is a large undertaking that requires systematic changes on both an organizational and an individual level – processes that are highly dependent on the local context and difficult to control. The implementation in this study is initiated by an external stakeholder, Närhälsan, and performed by a publicly procured company. As such, we as researchers have little control over the specifics of training and supervision, as well as over which PCCs participate in the project, how these are chosen, and their internal contexts and readiness for change. This means that the model fidelity categorization is an essential aspect – especially as many measurements and analyses are hierarchically dependent on each other. Patient outcomes (such as everyday functioning and satisfaction with care) may be partly dependent on organizational outcomes (such as waiting time until first visit) and they are both dependent on implementation outcomes (such as acceptance of and adherence to PCBH routines).

We have designed this study in an effort to evaluate the causal effects of PCBH despite these complex aspects. We have identified relevant measures and divided them into the three hierarchical levels described above. The data analysis plan has been designed to primarily utilize the randomized controlled design from both a per-protocol perspective (focusing on PCCs with successful implementation) and an intent-to-implement perspective (focusing on all PCCs in the EARLY implementation group regardless of which model fidelity category they reach). These analyses are complemented by secondary analyses based only on model fidelity and its association with outcomes, ignoring the randomized design but providing an opportunity of an equivalent of a dose-response analysis. Finally, in case we do not establish superiority for PCBH on the patient-level primary outcome, we will also execute non-inferiority analyses. In total, this results in a large number of planned analyses, but we deem this to be necessary to manage the complexities described above.

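### Analysis 5 sets mostly period 2 FID3 time against period 1 DELAYED time only, so part or nearly all of a change common to all centres is estimated as a fidelity effect; analysis 6 shares this to a lesser degree

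*Protocol article*

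**What the plan says.** The Data analysis plan lists six comparisons. The last two stand under the label "Adherence-response analyses (not controlled by randomization" and are worded "All PCCs, regardless of arm, when in FID3 during period 1 or 2, compared to PCCs in DELAYED during period 1.6.As (5), but compared to" all centres before FID3. The "6" inside that run is the list number of the sixth analysis. The comparator of analysis 5 is therefore DELAYED in period 1 only. That of analysis 6 is wider: "but compared to all PCCs before they reach FID3", with no limit to period 1.

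The aim is given as "the non-controlled (i.e., not comparing the randomized groups) relation between reaching adequate model fidelity and outcomes". The Discussion describes these analyses as "ignoring the randomized design but providing an opportunity of an equivalent of a dose-response analysis".

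On timing, Current trial status says "Implementation period 1 started in January 2022. Patients will be included until December 31st 2023", which is about 24 months. Design and overall procedure has period 2 begin 5 to 9 months after period 1 and allows it to be lengthened. On the model, Statistical tests says "Hierarchical Linear Models and Generalized Estimating Equations will be the primary statistical methods used" and adds that nesting will be respected; it lists no fixed effects for any analysis. The Sensitivity analyses section covers the fidelity cutoff and the timing of the pre-measure, not calendar time.

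**The concern.** Centres enter the trial outside PCBH and can reach FID3 only later, after training and supervision that runs over six months. FID3 status is therefore tied to calendar date. In analysis 5 the stated windows strengthen the tie. Exposed time can run to the end of inclusion, while comparator time stops when period 1 stops. DELAYED centres are compared largely with their own past, and the period 2 time of centres not yet at FID3, which could serve as a concurrent comparison, is left out.

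A change that reaches all centres (season, staffing, regional policy, case mix) then enters the fidelity estimate. The article mentions one candidate itself: its description of PCBH notes a general move in Swedish health care towards direct triage, which is also one of the planned PCBH changes. Such a move could shift waiting time, the primary organizational outcome, in every centre. A trend in one direction would create an apparent adherence-response; a trend in the other would hide a true one.

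**Working it through.** The plan gives no drift figure to reproduce, so the check asks what the stated windows do when fidelity has no effect.

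**Inputs from the article:** 17 centres (8 and 9), ICC 0.01, 476 patients analysed, period 1 of 5 to 9 months, inclusion over about 24 months.

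**Assumptions:** EARLY has the 8 centres; centres are of equal size with even recruitment; period 2 runs to the end of inclusion; FID3 is reached 3 to 9 months after start (mean 6); the common drift is linear at 0.2 SD per 24 months, or a 0.2 SD step at the start of period 2.

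**By hand, with period 1 of 7 months and FID3 at the mean of 6 months after start, in centre-months:**

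- FID3 time: EARLY, months 6 to 24, 8 × 18 = 144, midpoint 15. DELAYED, months 13 to 24, 9 × 11 = 99, midpoint 18.5. Mean date = (144 × 15 + 99 × 18.5) / 243 = 16.4 months.
- Comparator of analysis 5: DELAYED, months 0 to 7, mean date 3.5.
- Comparator of analysis 6: EARLY, months 0 to 6, 8 × 6 = 48, midpoint 3. DELAYED, months 0 to 13, 9 × 13 = 117, midpoint 6.5. Mean date = (48 × 3 + 117 × 6.5) / 165 = 5.5 months.

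Spurious effect under linear drift = (difference in mean date) × 0.2 / 24:

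- Analysis 5: (16.4 − 3.5) × 0.2 / 24 = 0.108 SD.
- Analysis 6: (16.4 − 5.5) × 0.2 / 24 = 0.091 SD.

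Spurious effect under the step = 0.2 × (period 2 share of exposed time − period 2 share of comparator time). FID3 time in period 1 is 8 × 1 = 8 of 243, or 3%.

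- Analysis 5: 0.2 × (0.97 − 0) = 0.19 SD.
- Analysis 6: the comparator's period 2 share is 9 × 6 / 165 = 0.33, so 0.2 × (0.97 − 0.33) = 0.13 SD.

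**By simulation** (FID3 dates drawn from the 3 to 9 month range, period 1 of 5, 7 or 9 months, inclusion over 24 months):

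| | Analysis 5 | Analysis 6 |
|---|---|---|
| Spurious effect, linear 0.2 SD | 0.10 to 0.12 SD | 0.09 to 0.10 SD (0.07 if a quarter of centres never reach FID3) |
| Spurious effect, 0.2 SD step | 0.18 to 0.20 SD | 0.09 to 0.12 SD |
| Concurrency | 1 to 11% of FID3 patients fall in period 1, alongside the comparator | 57 to 71% of pre-FID3 patients are seen after the first centre reaches FID3 |

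With 476 patients and the linear 0.2 SD drift, a two-sided 5% test without a time term rejects in about 10 to 19% of trials across the two analyses. At zero drift analysis 6 rejects in about 5%, and at 0.1 SD in 7 to 8%. If inclusion lasted only 14 months at the same rate of drift, the spurious effects would be about 0.06 SD (analysis 5) and 0.04 SD (analysis 6).

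**Can a model term alone repair analysis 5?** Not well. With its window unchanged, a linear time term leaves 0.09 to 0.19 SD of a 0.2 SD step. A period indicator inflates the variance of the contrast about 3- to 15-fold, because the data set holds no unexposed period 2 patients. In analysis 6 the corresponding figures are 0.00 to 0.05 SD and 1.3- to 1.8-fold.

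**The case against.** The strongest reply is that the article discloses the weakness. It labels both analyses as outside the randomisation and ranks them as "complemented by secondary analyses based only on model fidelity and its association with outcomes, ignoring the randomized design". That stands, and it lowers the priority. The label says that arms are not compared, though; it does not say that exposed and comparator time differ systematically by date, and it does not remove the bias.

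A second reply is that a journal article leaves model terms to an analysis plan, which is not shown. This stands for the model. A reader might infer that the analyses have no calendar-time term, but the article lists no fixed effects for any analysis, so it neither includes nor excludes one. It does not answer the window of analysis 5, which is fixed in the text and which a time term alone repairs poorly.

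Third, a reader might take analysis 6 for a plain before-and-after comparison. It is not: its comparator includes period 2 time of centres not yet at FID3.

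Fourth, patient scores analysed as change from the pre-measure would partly cancel a common shift in level. That is fair, and it makes the patient-outcome figures above an upper guide under that analysis. Waiting time has no such protection, but it was not simulated.

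**Conclusion.** The point holds for analysis 5 as a matter of its stated window, and in weaker form for analysis 6 as a request to state how calendar time is handled. With an assumed linear drift of 0.2 SD over 24 months, about half of the drift appears as a fidelity effect in analysis 5 and somewhat less in analysis 6. With a step at period 2, analysis 5 takes up almost all of it. These sizes rest on assumed drift and assumed FID3 dates; the article gives neither.

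Two stronger readings are not supported. One is that every common change is credited in full to fidelity: the share is partial under linear drift and depends on the shape of the trend. The other is that analyses 5 and 6 are the fallback if few EARLY centres reach FID3 in period 1, so that an artefact could become the main evidence. The Data analysis plan gives that role to analysis 2. Analysis 2 has a similar window imbalance (EARLY in both periods against DELAYED in period 1) and deserves its own check.

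Because these are disclosed, non-randomised secondary analyses, the priority is low.

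**What to change.** In the Data analysis plan, let analysis 5 also use all pre-FID3 time in period 2 as comparator, or drop it in favour of analysis 6. The widened analysis 5 would differ from analysis 6 only by leaving out EARLY pre-FID3 time in period 1, so keeping one of them loses little.

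In whichever is kept, fit a time-varying FID3 indicator, a PCC effect, and calendar time (for example quarter of inclusion) as a fixed effect, so that FID3 centres are contrasted with non-FID3 centres in the same calendar period. Keep the existing statement that the comparison is not randomised, and add that which centres reach FID3, and when, remains observational.

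In simulation with quarter-of-inclusion effects, the spurious estimate falls to 0.00 to 0.02 SD and rejection to about 3 to 7%. The cost is a wider interval: a standard error of about 0.14 to 0.18 SD with 476 patients, roughly 1.2-fold for analysis 5 and 1.5- to 1.8-fold for analysis 6. Only plan wording changes, since the analyses as defined already require inclusion dates and FID3 dates.
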